#### Management and quality of the data

All the data related to patient recruitment, the execution of the programme and the demographic characteristics of the users (age, sex, socioeconomic level) as well as the clinical variables (chronic health problems, biological and clinical parameters) will be obtained from the information extracted from the electronic health records of the Basque Health System. The Primary Care Research Unit of Bizkaia is explicitly authorised by the Healthcare Management of the Basque Health System to extract and use data from the electronic health records for research purposes. The coordination, process quality control and execution of the study, as well as management of data and ensuring its quality, are the responsibility of the Primary Care Research Unit of Bizkaia. The telephone interviews of the participants for the evaluation process of lifestyle changes will be carried out by trained professional interviewers, under the supervision of the research team. All the study data were treated anonymously and have been exclusively used for the objectives of the study. The confidentiality of personal data of participants was safeguarded at all times, in accordance with the organic law for personal data protection (15/1999 of December 13). Safety outcomes were not assessed because we did not anticipate any adverse effects due to the intervention given that it only involved physical activity and healthy diet promotion.

#### Sample size

As a worst case scenario regarding the main outcome variables for the optimisation of practices for the prevention of T2D, we hypothesise that we will obtain a rate 30% higher than a baseline level of 50% (that is, 65% in the sequential group vs 50% in the global group) in several of the outcome variables. Considering the participation of 9 centres, an alpha level of 0.05, and an intra-class correlation coefficient (ICC) at centre level of 0.03, we will need a minimum of 425 patients at high risk of developing T2D to be exposed to the prescription of a personalised plan for lifestyle change per group (850 in total) to achieve a statistical power of 80%, allowing for a possible loss of 20% of patients, in the comparison of the aforementioned process indicators related to exposure and execution of the intervention. This scenario is reasonably plausible assuming that 50% of the doctors lists in the centres agree to collaborate with this research and if we consider that, according to data from OSABIDE, an average attendance per year of 875 patients over 45 years of age with prediabetes (baseline glucose ≥110 mg/dl) per group (175 per centre). For exploring a possible modification of clinical outcomes from the prescription of lifestyle changes, namely, a 5% loss of body weight, attributable to the creation of the community of practice, we need 616 patients (308 per group) to achieve a power of 80% to reject the null hypothesis H_0_:p1 = p2 using a bilateral chi-squared test for two independent samples with a level of significance of 5%, considering that 10% of patients will attain such change in one of the groups and 35% in the other, assuming an ICC of 0.03 and a possible loss of 10% of patients at 12 months.

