## Background

The dramatic increase in the rates of type 2 diabetes mellitus (T2D) and associated complications has made it a major health problem worldwide [1]. Despite the growing evidence provided by landmark T2D prevention trials and several translational studies assessing both the efficacy and effectiveness of healthy lifestyle prevention interventions in clinical and community settings [2–12], the actual translation and integration of primary prevention programmes in routine clinical practice remains an unsolved challenge. Indeed, currently, in the real context of the provision of services seeking to prevent T2D in the Basque Health Service (Osakidetza), only 30% of patients at high risk of developing this disease receive some type of intervention focused on preventive advice.

In the PreDe multicentre trial conducted in 14 Osakidetza PHC centres, it was shown that an intervention promoting healthy lifestyles among patients at high risk of developing the disease succeeded in reducing the incidence of T2D by almost a third (32%) [12]. Nevertheless, despite having identified an intervention that is potentially effective for preventing T2D in PHC, the passive implementation strategy used for guiding the translation and adoption of the intervention in a routine clinical context by our health professionals has not achieved feasible and sustainable deployment, with low levels of adoption by clinicians, limited population coverage, failure to integrate the intervention into practice, and lack of continuity at the end of the project, among other problems. The factors identified by the professionals as the main barriers that constrained the feasibility of integration of the programme under routine conditions in the centres and implied that it would not be sustainable were the lack of participation and commitment from the staff of the centres in the context of time pressures and heavy workloads. These two factors, in turn, limited the organisation of operational elements required for putting the programme and its components into practice, in an environment with few incentives and an overload of corporate initiatives [13].

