### Random allocation

The implementation strategy to facilitate the adoption of the recommended clinical intervention for T2D prevention will be common to the two comparison groups (see the following section). In order to distinguish and isolate any effects of the strategy used for the creation of the multidisciplinary community of practice, the centres will be randomly allocated to one of the comparison groups: five centres to the sequential strategy and the other four to the global strategy. This random allocation will be carried out by the members of our research unit not involved in this project, using a computer-generated random number sequence obtained before starting the trial. Given that the new programme is an optimisation of T2D prevention activities already offered by the Basque Health Service, it is expected that participating patients will be blinded to group allocation.

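### The printed inputs (65% vs 50%, nine centres split 5:4, ICC 0.03, 425 per group less 20%) give about 48–62% power for a two-sided comparison without baseline adjustment, not the stated 80%

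*Protocol article*

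**What the plan says.** The Sample size section of the protocol article sets out a full calculation for the process indicators. The rates compared are "65% in the sequential group vs 50% in the global group". The design inputs are "Considering the participation of 9 centres, an alpha level of 0.05, and an intra-class correlation coefficient (ICC) at centre level of 0.03". The output is at least 425 patients per group (850 in total) "to achieve a statistical power of 80%, allowing for a possible loss of 20% of patients".

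The Random allocation section fixes the split of the nine centres: "five centres to the sequential strategy and the other four to the global strategy".

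This calculation does not say whether the test is one- or two-sided. The weight-loss calculation later in the same section is two-sided at 5%, and the Analysis section reports 95% confidence intervals.

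**The concern.** In a cluster trial with few centres, between-centre variation sets a floor on the standard error that extra patients cannot lower. With four or five centres per arm and an ICC of 0.03, that floor is high for a 15-point difference. The stated 425 per group looks too small for the design effect these inputs imply.

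This is the only power statement for the experimental comparison of the main outcomes. If it is wrong, readers will judge an inconclusive result against 80% when the design, as calculated, has little better than an even chance of detecting the planned difference. The Analysis section adds to the problem: it expects every comparison to be statistically significant because more than 20,000 patients are available, which overlooks that centres, not patients, limit precision.

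**Working it through.** **Inputs.** Rates 0.65 and 0.50, alpha 0.05, ICC 0.03, nine centres, 425 per group and 20% loss (Sample size); 5 and 4 centres (Random allocation). Assumptions: two-sided test, equal centre sizes within an arm, no baseline adjustment. Evaluable patients: 425 × 0.8 = 340 per group.

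**1. Sample size without clustering.** With mean rate 0.575:

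n₀ = [1.960·√(2·0.575·0.425) + 0.842·√(0.65·0.35 + 0.50·0.50)]² / 0.15² = 169.3, so 170 per group.

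**2. What the plan's figure implies.** 340 / 169.3 is a design effect of about 2.0. Setting 1 + (m − 1)·0.03 = 2.0 gives m of about 34 to 35 patients per centre, or roughly 10 centres per group. The design has 5 and 4. The stated figure comes close to 80% if nine centres are counted in *each* group (m = 37.8, design effect 2.10, effective n 162, power about 78%). That is only an inference from the arithmetic.

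**3. Power with 340 evaluable per group, 5 vs 4 centres.**
- Patients per centre: 340/5 = 68 and 340/4 = 85.
- Design effects: 1 + 67·0.03 = 3.01 and 1 + 84·0.03 = 3.52.
- Effective n: 340/3.01 = 113.0 and 340/3.52 = 96.6.
- SE = √(0.2275/113.0 + 0.25/96.6) = 0.0678, and 0.15/0.0678 = 2.21.
- Normal: Φ(2.21 − 1.96) = 0.60. Non-central t with 9 − 2 = 7 df (critical value 2.365): 0.48.

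**4. Power with all 425 per group.** Design effects 3.52 and 4.16; effective n 120.7 and 102.2; SE 0.0658; ratio 2.28. Power is about 62% (normal) or 50% (t).

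**5. Ceiling with unlimited patients.** Effective n per arm tends to k/ICC: 5/0.03 = 166.7 and 4/0.03 = 133.3, both below 170. SE = √(0.2275/166.7 + 0.25/133.3) = 0.0569; ratio 2.64. Power is about 75% (normal) or 62% (t). At 10,000 patients per group it is 74% or 61%.

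**6. Variants.**

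| Setting | Normal | t |
|---|---|---|
| One-sided, 340 per group | 71% | 64% |
| One-sided, 425 per group | about 74% | 66% |
| One-sided, unlimited patients | 84% | 77% |
| Two-sided, 340 per group, ICC 0.01 | about 86% | 74% |
| Two-sided, 340 per group, ICC 0.05 | 45% | 35% |
| Two-sided, 340 per group, five centres in each arm | about 63% | 53% |

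The five-per-arm row is included because the attendance figures in Sample size (875 per group, 175 per centre) imply 875/175 = 5 centres per group.

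**7. Difference detectable with 80% power** (two-sided, 340 per group, ICC 0.03): 50% vs about 69% (normal) or 72% (t), that is 19 to 22 points.

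**The case against.** **Sidedness.** The section gives only "an alpha level of 0.05" for this calculation, and the Background states a directional hypothesis. A reader might infer that 80% power is out of reach at any number of patients whatever the test. The document does not support that. With a one-sided test and a normal approximation the ceiling is about 84%. The two-sided reading is likelier, given the companion calculation and the 95% intervals, but it is not stated. What survives is that 425 per group falls short on either reading.

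**Baseline adjustment.** Table 2 collects the coverage and execution indicators at baseline as well as at 12 months, and the Analysis section plans pre-post differences and adjusted multilevel models. A reader might infer from the figures above that the planned analysis itself has only 48–62% power. That does not follow. If centre baseline rates are used and correlate r with follow-up rates, the residual ICC could be about 0.03(1 − r²). The documents give no r. As an assumed range with 340 per group, r = 0.5, 0.75 and 0.9 give 68%, 81% and 92% (normal) or 55%, 68% and 82% (t). This objection stands as a limit on the finding, but it does not rescue the printed calculation, which uses 0.03 and has no such term.

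**The baseline rate.** The calculation is introduced with "As a worst case scenario regarding the main outcome variables", and the Background reports that "only 30% of patients at high risk of developing this disease receive some type of intervention focused on preventive advice". A reader might infer that 39% vs 30% is the proper scenario. It is not the plan's scenario. The 30% describes current usual care for preventive advice, whereas the 50% is assigned to the global arm, which receives training, leadership and facilitation.

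**Consequences.** No equivalence conclusion is planned, the Analysis section stresses the size of differences, and the Discussion lists the small number of centres as a limitation, though for generalisability and not for power. A misreading of a null result is therefore a risk, not something the plan invites.

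**Conclusion.** The point holds as a mismatch between the section's inputs and its output. Two-sided, 5 vs 4 centres, ICC 0.03 and no baseline adjustment: power is about 60% or 48% with 340 per group and about 62% or 50% with 425, against 80% stated, a shortfall of roughly 20 to 30 points. On those assumptions adding patients cannot close the gap, since the ceiling is about 75% or 62%. One-sided, the stated sample still falls short.

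The normal figures are the favourable end of each pair. The t figures with 7 df reflect how little information nine centres carry about between-centre variance. The 20% loss is taken as 425 × 0.8; a lighter reading of the loss falls between the 340 and 425 results. This is an error in a complete, printed calculation, so it cannot be set aside as detail left to an analysis plan.

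**What to change.** Reword the power statement in Sample size:

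- State whether the test is one- or two-sided.
- Replace the 80% claim with what the design delivers, for example: with nine centres (5:4), ICC 0.03 and a two-sided 5% test without baseline adjustment, power for 65% vs 50% is about 48–62% and cannot reach 80% by adding patients; the difference detectable with 80% power is 50% vs about 69% (normal) or 72% (t, 7 df).
- Give the sensitivity to the ICC with 340 evaluable per group: about 86% or 74% at 0.01, and 45% or 35% at 0.05.
- If adjustment for centre baseline rates is relied on to recover power, state the assumed residual ICC and its basis.

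The cost is a rewritten paragraph and a less favourable power figure. Enrolment, outcomes and conduct stay as they are.

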#### Analysis

All the analyses will be carried out on an intention-to-treat basis and then exploratory analysis will be performed by protocol and subgroup. We will estimate the absolute and relative pre-post intra-centre and between groups differences and the 95% confidence intervals using multi-level logistic regression for dichotomous variables (e.g. proportion of patients with a prescription for lifestyle change). As the sample size for evaluating the implementation objectives is over 20,000 patients, all the comparisons will be significant from a statistical point of view, and hence, emphasis will be placed on the magnitude of these differences, following the Cohen categories based on standardised differences: < 0.5; ≥ 0.5 to ≤ 0.8 and > 0.8 being considered to indicate small, moderate and large effects respectively. Comparisons will be adjusted for potential confounding factors, through stratified analysis and the inclusion of such factors in the regression models following forward and backward strategies guided by the stratified analyses.

To assess the maintenance of implementation outcomes through the 24-month follow-up, mixed-effect generalised longitudinal models will be built with fixed effects (intervention group, effect of time on monthly process indicators and interaction time-intervention) and random effects on the intercept and the slope (for each subject, doctor-centre). Said models will be adjusted for the potential confounding variables, following a forward strategy guided by the stratified analyses. Through these statistical models, we will take into account the intra-class correlation (between doctor-centre) and the hierarchical nature of data: patients nested by medical consultations and these grouped by health centre. All the analyses were carried out using SAS statistical software.

Regarding the secondary outcome variables, the percentages (e.g. % of patients who meet recommendations on physical activity) were compared using chi-square or non-parametric tests. Quantitative variables were compared using t-tests (comparison of the means). For these outcome measures, pre-post differences and differences between study groups will be estimated, and 95% confidence intervals (CIs) will be calculated on an intention-to-treat basis. Stratified analysis will be performed, mixed-effects generalised models will be built to estimate the differences between the groups adjusted for factors that confound or moderate the effect of the intervention (baseline demographic and clinical characteristics) and adjusted differences, adjusted odds ratios (ORs) and 95% CIs will be calculated at the patient level, taking into account the hierarchical and multicentre structure of data. To explore a potential modifying effect of the intervention on clinical outcomes obtained attributable to the procedure for creating the interprofessional community of practice, we will conduct comparisons by intervention protocol between groups using matching by propensity scores calculated on the basis of the characteristics of patients recorded in their health record. This will permit us to analyse the association between the actual intervention dose received (assessment of lifestyle habits, assessment of habits plus advice, and assessment of habits plus advice plus prescription) and the event of interest (change in lifestyle habits or weight loss) as a function of one or other engagement procedure, pairing patients participating in one or another comparison group in a 1:1 ratio on the basis of them having a similar probability of having received said treatment or intervention dose.

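### The 12-month comparison is fixed only as a multi-level logistic regression and expects its precision from over 20,000 patients; it needs a centre-by-period term and a small-sample reference for nine centres

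*Protocol article*

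**What the plan says.** All points are from the protocol article.

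- **Analysis, first paragraph (12-month outcomes).** "We will estimate the absolute and relative pre-post intra-centre and between groups differences and the 95% confidence intervals using multi-level logistic regression" for dichotomous variables. No random effects are listed.
- **Same paragraph.** Because "the sample size for evaluating the implementation objectives is over 20,000 patients, all the comparisons will be significant", the emphasis moves to the size of differences on standardised-difference categories. The 95% confidence intervals are still to be reported.
- **Analysis, second paragraph (24-month maintenance).** Mixed models with a time-by-intervention interaction and "random effects on the intercept and the slope (for each subject, doctor-centre"). The hierarchy, "patients nested by medical consultations and these grouped by health centre", is described here, in a sentence that refers back to these models.
- **Random allocation.** "five centres to the sequential strategy and the other four to the global strategy".
- **Sample size.** "Considering the participation of 9 centres", with "an alpha level of 0.05, and an intra-class correlation coefficient (ICC) at centre level of 0.03".
- **Table 2.** Coverage and execution indicators are measured at baseline and 12 months. Spreading indicators are measured at baseline, 12 and 24 months.

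**The concern.** The unit of randomisation is the centre, and there are nine. In a pre-post comparison a random centre intercept absorbs how high or low a centre starts, and then drops out of the arm-by-period contrast. If nothing in the model lets centres change by different amounts, that contrast is judged against patient-level noise alone. The hypothesis tested is then that every centre changed equally, not that the two strategies produce the same change on average.

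Unequal change is to be expected in this trial. Table 2 makes the coverage indicator depend on the screening approach each centre picks. The Implementation strategy section has each centre standardise its own programme. The third specific objective looks for organisational factors behind success. The Discussion lists staff rotation as a centre-level threat.

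The sentence about universal significance makes this more than an unlisted detail. It can be true only if patients, not centres, set the precision. At stake is whether an ordinary difference in drift between five and four centres gets an interval that excludes zero and is read as an effect of the order in which professionals were engaged.

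**Working it through.** **The plan's own figure.** For 65% vs 50%, two-sided 5% and 80% power, the unclustered size is 170 per group. With 170/5 = 34 per centre and ICC 0.03, the design effect is 1 + 33 × 0.03 = 1.99. Then 170 × 1.99 = 338, and 338/0.8 = 423, against the stated 425. So the sample size does count centre-level clustering. The question is whether the analysis does.

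**Inputs from the article.** 5 and 4 centres; ICC 0.03; 850/9 ≈ 94 high-risk patients per centre (planned minimum) or 175 (expected attendance); 20,000/9 ≈ 2,222 per centre for the large denominators; 50% planning rate.

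**Assumed, not in the article.** SD of the centre-specific pre-post change, s = 0.1 to 0.3 logit. On the logit scale ICC 0.03 means a centre variance of (0.03/0.97) × π²/3 = 0.1017. The implied correlation between a centre's two periods is 1 − s²/(2 × 0.1017): 0.95, 0.80 and 0.56 for s = 0.1, 0.2 and 0.3. Centres are taken as equal in size, the two periods' patients as independent, and m as the number per centre in each period.

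**Formula.** With intercepts only, the variance credited to one centre's change is v = 2/(m·p(1−p)). The true variance is v + s². The true standard error therefore exceeds the model's by k = √(1 + s²/v), and a nominal 5% test has size 2 × [1 − Φ(1.96/k)].

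At p = 0.5:

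| m | v | s = 0 | s = 0.1 | s = 0.2 | s = 0.3 |
|---|---|---|---|---|---|
| 94 | 0.0851 | 5% | 6.4% | 10.6% | 17.2% |
| 175 | 0.0457 | 5% | 7.6% | 15.2% | 25.5% |
| 2,222 | 0.0036 | 5% | 31% | 57% | 70% |

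At p = 0.3 and m = 2,222, v = 2/(2,222 × 0.21) = 0.0043 and the sizes are 28%, 54% and 68%.

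**Simulation, 5 vs 4 centres, equal strategies.** Intercept-only inference rejected about 27% to 69% at 2,222 and about 6% to 24% at 94 to 175 over s = 0.1 to 0.3. Fitted random-intercept logistic models at 2,222 gave 3%, 26.5%, 52.5% and 68.5% for between-period correlations of 1, 0.95, 0.8 and 0.5 (200 runs each). A t-test with 7 df on the nine centre changes stayed near 5% throughout.

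**Interval width.** k is 1.9 to 5.1 at 2,222, but only 1.06 to 1.7 at 94 to 175.

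**Can every comparison be significant?** With s = 0.2, the standard error of the arm difference in change cannot fall below 0.2 × √(1/5 + 1/4) = 0.134 logit, however many patients there are. With 7 df (critical value 2.365) a difference must exceed 0.317 logit, about 8 points from 50%. Using patient noise alone, the standard error at 2,222 is √(2 × 0.25/2,222 × 0.45) = 1.0 point, so about 2 points would suffice.

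**Comparison at 12 months only.** The intercept no longer cancels, and at ICC 0.03 the floor is √(0.25 × 0.03 × 0.45) = 5.8 points. Significance needs about 11 points by z, or 2.365 × 5.8 ≈ 14 points with 7 df. If the z is used, the size is P(|t₇| > 1.96) ≈ 9% with a 7-df variance estimate. With a maximum-likelihood variance (divisor 9) it is P(|t₇| > 1.96 × √(7/9)) ≈ 13%. Simulation gave about 12%.

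**The case against.** The strongest reply is that the article never specifies an intercept-only model. A reader might infer that it does, because the slope appears only in the 24-month paragraph. But the nesting description sits in that same paragraph, so one cannot carry the hierarchy over to the 12-month model and leave the slope behind. Listing random effects is also commonly left to a full protocol or analysis plan. The promise of intra-centre differences could even mean a separate change for each centre. And the sample size compares 65% with 50%, so the between-group contrast may be at 12 months only, where the intercept does not cancel. All of this stands: the omission is inferred.

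A reader might also infer that the test rejects far above 5% on all main outcomes. That is not supported either. The SD of centre change is not in the article, inflation is nil if it is zero, and it is modest for the high-risk execution outcomes. Nor does the article say that the 20,000 are per period. If they cover both, m ≈ 1,111, v = 2/(1,111 × 0.25) = 0.0072, and the size at p = 0.5 is about 20% (s = 0.1) to 59% (s = 0.3).

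Lastly, the plan stresses magnitude over p-values. With s = 0.3 the standard error of drift is 0.3 × √0.45 = 0.20 logit. A chance difference of 1.96 × 0.20 = 0.39 logit is about 0.39 × √3/π = 0.22 standardised, which the plan would call small. That limits the consequence but does not remove it, because a small effect whose interval wrongly excludes zero is still read as an effect.

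What the reply does not answer is the sentence on universal significance. Neither a model with centre-specific change nor a post-only comparison respecting ICC 0.03 would make every difference significant with nine centres.

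**Conclusion.** The point holds in a limited form. The article leaves the error term of its main 12-month comparison open and states an expectation that fits only patient-level precision. Under an intercept-only pre-post model, the false-positive rate with equal strategies is about 27% to 69% for outcomes with the largest denominators (coverage and spreading) and about 6% to 24% for high-risk execution outcomes. These figures rest on an assumed SD of centre change of 0.1 to 0.3 logit and on reading the 20,000 as per period. With equal change in all centres there is no inflation. Under the alternative post-only reading, a large-sample z test on nine centres still rejects about 12%. Either way the 12-month analysis needs an explicit centre-level error term and a small-sample reference. The article does not establish that the wrong model has been chosen.

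**What to change.** 1. State for the 12-month comparison a random centre-by-period effect (a centre-specific pre-post change), matching the slope already named for the 24-month model. Say also whether the main contrast is the arm-by-period term or the 12-month difference.
2. Test it and form its interval with a small-sample reference: t with 7 df, or Kenward-Roger.
3. Report the nine centre-level changes alongside, 5 vs 4, by t-test or by exact permutation over the C(9,4) = 126 possible allocations. The smallest attainable permutation p-value is 1/126 ≈ 0.008, so the 5% level can be reached.
4. Withdraw the statement that all comparisons will be significant.

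The cost is one random-effect term and a degrees-of-freedom option in SAS, with no new data. The drawback is wider confidence intervals: on the figures above, differences below roughly 4 to 12 points from 50% (2.365 × s × √0.45 = 0.16 to 0.48 logit for s = 0.1 to 0.3) would not reach significance even in the largest denominators.
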